## Abstract

Human Papillomavirus (HPV) is causally associated with cervical cancer and precancerous lesions (dysplasias) of the cervix. The treatment of choice for low-grade lesions is monitoring with no-treatment, because the majority of them will regress spontaneously. However, this wait-and-see approach can be assisted by nutritional supplements for immune support, like Moducare. The hypothesis of the trial is that Moducare can enhance the natural regression of CIN1. MODUCIN1 is a prospective, open-label, randomized trial where eligible patients will be randomized (1:1) to either the wait-and-see approach (control arm) or to the six months oral administration of Moducare capsules. The main inclusion criterion is newly histologically proven CIN1 and the main exclusion criterion is any previous cervical intraepithelial neoplasia with or without treatment or history of pelvic malignancy. The primary objective is to compare the regression rates of low-grade cervical intraepithelial neoplasia (CIN1) between the two groups: Wait-and-see approach and Moducare. The sample size is estimated at 182 eligible patients, while accrual is expected to last one year. The primary endpoint is expected to be reached after six months from last patient enrollment. The Trial Registration Number is NCT07379905.

## Introduction

Human papillomavirus (HPV) is causally associated with virtually all cases of cervical cancer and its precursor lesions under the term cervical intraepithelial neoplasia (CIN), representing one of the strongest causal relationships documented in cancer epidemiology [1]. HPV-induced cervical dysplasia arises predominantly within the transformation zone and is classified histologically into low-grade cervical intraepithelial neoplasia (CIN1) and high-grade cervical intraepithelial neoplasia (CIN2/CIN3) lesions according to the Bethesda classification system, with the latter warranting excisional treatment. CIN1 lesions demonstrate transient productive HPV infection and spontaneous regression occurs in approximately 60% of cases under monitoring, while progression to CIN2 + occurs in only 11% and to cervical cancer in less than 0.5% of patients [2]. These favorable natural history data underpin current international guidelines that endorse active surveillance instead of immediate intervention for CIN1. Nevertheless, long-term follow-up data challenge the notion that the risk of progression for low grade cervical intraepithelial lesions is uniformly low. A nationwide, registry-based cohort study [3] demonstrated that the five-year cumulative incidence of CIN2+ among women with histologically proven CIN1 reaches 19%, rising to 25–26% in women with high-grade cytology or HPV16/18-positive status. These findings highlight a clinically significant subset of CIN1 patients at substantial risk of disease progression and underscore the need for interventions capable of enhancing the spontaneous regression rate of the wait-and-see approach alone.

The immunological environment of the cervical epithelium is a major determinant of whether HPV infection persists or is cleared, with effective viral clearance depending on a robust cell-mediated Th1-type immune response [4]. Plant sterols and sterolins, phytochemicals of which beta-sitosterol (BSS) and its glucoside (BSSG) are the principal bioactive constituents, have been shown to specifically modulate T-helper lymphocyte activity, selectively enhancing Th1-associated cytokines (interleukin-2, interferon-gamma) while suppressing the Th2-associated cytokine interleukin-4, thereby restoring immunological balance in conditions of chronic viral infection [5]. Flow cytometric studies in HIV-infected patients confirmed that administration of the BSS-BSSG mixture shifted a pathological Th2-predominant response toward a protective Th1 profile, mirroring the pattern observed in healthy controls [6]. Clinically, this immunomodulatory mechanism has been previously tested in the management of HPV-associated anogenital warts, according to the results of a randomized trial demonstrated that BSS-BSSG supplementation (Moducare) significantly improved the clearance of anogenital warts when combined with cryotherapy. It was found that lesion-free rates of 79.4% were observed at combination arm (cryotherapy plus six month Moducare) versus 61.7% at cryotherapy only arm [7].

Based on the fact that the underlying mechanism of promoting the cellular immunity against persistent HPV is directly relevant to the pathogenesis of CIN1, there is a compelling biological rationale to evaluate Moducare for this indication. Therefore, the MODUCIN-1 trial is designed to test the hypothesis that adjunctive immunomodulatory treatment can meaningfully increase and robust the rate of histological regression of CIN1 compared with surveillance alone. It is a prospective, open-label, randomized controlled trial that will allocate 182 women with histologically proven CIN1 in a 1:1 ratio to either a Wait-and-See group (control arm) or to six-month oral Moducare supplementation group (intervention arm), with the primary endpoint of CIN1 regression at six months.

## Materials and methods

### Trial design

This is a prospective, open-label, randomized trial, with no patient or public involvement. Patients are eligible for enrollment irrespective of any HPV status and Pap test result. Participants will be included in the study with histologically proven CIN1, after colposcopy-directed cervical biopsies. During colposcopy, the cervix is divided into four quartiles and based on the location of suspicious acetowhite areas, one biopsy per quartile is obtained. Patients will undergo randomization into the following two groups: Wait-and-see approach with active monitoring, designed as control arm A, or six months treatment with oral capsules of Moducare, designed as intervention arm B. The participant timeline and trial scheme are presented in Fig 1 and Fig 2, respectively.

**Fig 1 pone.0353119.g001:**
[figure not shown]
MODUCIN1 participant timeline (SPIRIT Schedule).

**Fig 2 pone.0353119.g002:**
[figure not shown]
MODUCIN1 trial scheme.

After randomization, patients in both groups will undergo follow-up for at least one year, with two scheduled visits at six and twelve months. At these time points participants will undergo colposcopy-directed cervical biopsies from the cervical quartiles that were predefined as suspicious from the first colposcopy at randomization. If a suspicious acetowhite area at another previous normal appearing quartile is identified a colposcopy-directed cervical biopsy would be also obtained. Similarly to the first colposcopy, one biopsy per quartile will be taken.

The monitoring/treatment plan for each arm is in detail described below.

Control arm A: Patients in the wait-and-see approach will undergo active monitoring with colposcopy-directed biopsies at six and twelve months after randomization.Intervention arm B: Patients in the Moducare group will undergo a six-month treatment with Moducare oral capsules. The predefined dosage will be two capsules, three times per day for the first month, followed by one capsule, three times per day for the remaining five months. Moducare is classified as a natural dietary supplement, designed as an immune support supplement containing a patented blend of plant sterols and sterolins, primarily beta-sitosterol and beta-sitosterol glucoside, derived from plant sources.

Endocervical curettage (ECC) is optional together with the colposcopy-directed cervical biopsies, during colposcopy at all three time points (randomization, six- and twelve-month visits) in cases with transformation zone type III. During follow-up visits pap test and HPV-DNA or RNA tests are allowed according to national and international guidelines, at the attending physician’s discretion. In case of modification in the treatment plan in either arm (Moducare dose change, participant request or disease progression to CIN3), the patient will be dropped out of the trial. The setting of the trial is a tertiary, academic center, certified by ESGO for Gynecological Oncology training, with a fully equipped Colposcopy Unit and adequate workload in order to reach the needed sample size. All patients will be treated by three gynecological oncologist, certified in colposcopy from the Hellenic Society for Colposcopy and Cervical Pathology (HSCCP) and all results will be centrally reviewed by the director of the Colposcopy Unit, who will monitor data collection (at six months after randomization), perform an interim analyses and could decide to terminate the trial. The trial has been approved by the local Scientific Committee and it is registered on clinicaltrials.gov (NCT07379905).

### Study population

It is estimated that the total number of participants that will be enrolled in the trial and randomized to the two arms is 182. The major inclusion criterion is histologically confirmed only low-grade cervical intraepithelial neoplasia (CIN1), with any HPV status and test pap results, while the major exclusion criterion is inadequate colposcopy due to vaginal stenosis or other anatomical reasons with no visible suspicious acetowhite lesions on the cervix and CIN1 result from the endocervical curettage (ECC) in cases with transformation zone type III. All patients will be assessed for the inclusion and exclusion criteria of MODUCIN1 trial. Those criteria are in detail described in Table 1.

**Table 1 pone.0353119.t001:** Inclusion and Exclusion criteria.

**Inclusion criteria**	Age 18–85 years old
	ECOG Performance status 0–1
	Histologically proven low-grade cervical intraepithelial neoplasia (CIN1)
	Any Pap test result
	Any HPV status (negative, positive: high or low risk)
**Exclusion criteria**	Pregnancy
	Low likelihood of patient compliance to treatment protocol and follow-up
	Inadequate colposcopy
	Previous operation to the cervix
	Previous pelvic malignancy
	Previous history of histologically proven CIN1, at least before 12 months.
	Previous histologically proven with or without treatment high-grade cervical intraepithelial neoplasia (CIN2, CIN3)
	Hypersensitivity to trial medication

### Trial endpoints

The primary endpoint of the trial is to compare the regression rate of low-grade cervical intraepithelial neoplasia (CIN1), between the two arms: Wait-and-see control arm and Moducare intervention arm, at six months after randomization. Furthermore, the secondary endpoints include the comparison of regression rate of CIN1 at twelve months from randomization, the progression rate of CIN1 at six and twelve months after randomization and for safety analysis the intervention (Moducare) related adverse events at six months after randomization. All comparisons will be made between the above-mentioned arms of the trial.

### Sample size

For power analysis of the trial a two-sided alpha level of 0.05, a statistical power of 80% and accounted for a 10% drop-out rate. Based on the results of a large recent meta-analysis [2] the spontaneous regression rate of low-grade cervical intraepithelial neoplasia (CIN1) of the Wait-and-see approach was set at 60% and in order to achieve a clinically important increase of at least 20%, the regression rate of Moducare was set at 80%, since robust RCTs are absent. The sample size was calculated using RStudio (V 4.3.3), applying the chi-square test formula for comparison of two independent proportions. Accordingly, we plan to enroll approximately 182 patients to account for anticipated dropouts and maintain the integrity of the primary endpoint analysis.

### Randomization

The primary block randomization with a 1:1 allocation ratio and a fixed block size of 2 will be used to assign each participant either to control arm A (Wai-and-see) or intervention arm B (Moducare). The randomization list will be generated in R (version 4.5.1) using the randomizeR package [8]. After confirming that a candidate participant fulfils all eligibility criteria, the investigator will access the randomization system to obtain the next available randomization code and the corresponding preassigned study arm for that participant.

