Should the trial confirm our hypothesis, the implications for clinical practice would be substantial. Currently, the management of CIN1 relies exclusively on passive monitoring, which, despite its favorable overall natural history, leaves a clinically significant subset of patients at risk of progression, particularly those with HPV16/18-positive status, where the five-year cumulative incidence of CIN2 + can reach 25–26% [3]. The incorporation of an immunomodulatory supplement into the surveillance strategy could represent a paradigm shift in the management of low-grade cervical dysplasia, offering a non-invasive, well-tolerated intervention that actively promotes lesion regression. This approach could reduce the psychological burden associated with prolonged surveillance and decrease the need for subsequent excisional procedures.

On the other hand, some limitations of the MODUCIN1 trial should be acknowledged. The open-label design introduces the potential for performance and detection bias, as neither participants nor investigators are blinded to group allocation. While a placebo-controlled design would have been methodologically preferable, it was not feasible in the context of a dietary supplement trial where a truly inert placebo matching the appearance, taste, and dosing regimen of Moducare capsules was not available. Nevertheless, the use of an objective histological endpoint, assessed by colposcopy-directed biopsies that were centrally reviewed by the director of the Colposcopy Unit, mitigates the impact of observer bias on the primary outcome. Furthermore, the fact that pathological assessment of biopsy specimens is inherently blinded to treatment allocation provides an additional layer of objectivity.

Moreover, the six-month primary endpoint, while clinically practical and aligned with standard follow-up intervals for CIN1, may not capture the full trajectory of treatment effect, as some CIN1 lesions require longer periods for regression. The twelve-month secondary endpoint assessment partially addresses this limitation. Finally, adherence to a six-month oral supplement regimen is inherently challenging in dietary supplement trials [10], and the absence of an objective biomarker to confirm supplement intake (such as serum beta-sitosterol levels) means that treatment adherence will rely on patient self-report and capsule counting.

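### Blocks fixed at size 2 in an open-label, single-centre trial let half of the allocations be deduced before eligibility is judged

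*Protocol article*

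**What the plan says.** The Randomization section says that "block randomization with a 1:1 allocation ratio and a fixed block size of 2 will be used". After eligibility has been confirmed, "the investigator will access the randomization system to obtain the next available randomization code and the corresponding preassigned study arm". No stratification and no variation in block size is described.

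The Trial design section describes one site ("The setting of the trial is a tertiary, academic center") and a small clinical team ("All patients will be treated by three gynecological oncologist"). The Discussion lists open-label conduct as a limitation and says that "neither participants nor investigators are blinded to group allocation". It names performance and detection bias as the consequences; selection bias is not mentioned. One exclusion criterion in Table 1 is a judgement made at enrolment: "Low likelihood of patient compliance to treatment protocol and follow-up".

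**The concern.** A balanced block of 2 holds one woman per arm, so the first allocation in a pair fixes the second. In a blinded trial this would matter little, because nobody recruiting would know the first allocation. Here the recruiters know each arm once it is assigned, there are only three of them in one unit, and the block size is in print. A clinician who knows what the last woman received, and that she opened a pair, knows the arm of the next woman before deciding whether she is eligible, whether to approach her, or whether to wait for another candidate. The judgement on likely compliance gives room for this without any breach of the protocol, and it need not be deliberate.

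If enrolment into known slots depends on prognosis, the arms differ at baseline. Intention-to-treat analysis keeps the groups as they were formed and cannot correct how they were formed. The primary comparison is an unadjusted chi-square or Fisher test. The safeguards cited in the Discussion (a histological endpoint and pathologists unaware of allocation) protect outcome assessment, not entry into the arms.

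**Working it through.** **Inputs from the article.** Blocks of 2 at 1:1 (Randomization); regression of 60% and 80%, two-sided alpha 0.05, power 80%, 10% drop-out and 182 patients (Sample size). One list for the whole centre is assumed, since no stratification is mentioned.

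**The plan's own figure.** n per arm = [1.960·√(2·0.7·0.3) + 0.8416·√(0.6·0.4 + 0.8·0.2)]² / 0.2² = 81.22. Then 81.22/0.9 = 90.25, so 91 per arm and 182 in total. The stated size is reproduced and is not affected by this point.

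**Predictability.** 182/2 = 91 blocks. The first slot of each is a fair coin; the second is determined. Certain slots: 91/182 = 50%. Expected correct guesses: (0.5 + 1)/2 = 75%.

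**Illustration of bias (assumed; no such figures are in the article).** Suppose no true effect and two equal groups of women, recognisable at enrolment, with 70% and 50% regression, which average the plan's 60%. Recruiters steer a fraction f of the known slots, better-prognosis women to one arm and the others to the other arm. Half of each arm sits in known slots, so the arms have expected rates of 0.60 ± 0.10·0.5·f and the false difference is 0.10·f. Rejection probabilities are exact for the uncorrected chi-square test at 91 per arm.

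| Known slots steered | Rates | False difference | Type I error |
|---|---|---|---|
| none | 60% vs 60% | 0 | 0.05 |
| a quarter | 61.25% vs 58.75% | 2.5 points | 0.064 |
| half | 62.5% vs 57.5% | 5 points | 0.106 |
| all | 65% vs 55% | 10 points | 0.282 |

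Normal-approximation check of the last row: the critical difference is 1.960·√(2·0.24/91) = 0.1423; the standard error at 65% and 55% is √((0.2275 + 0.2475)/91) = 0.0723; (0.1423 − 0.10)/0.0723 = 0.586, with an upper tail of 0.279.

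**Range over the assumed gap.** With all known slots steered, the false difference is half the prognostic gap. Gaps of 10, 20 and 30 points give 5, 10 and 15 points, and type I errors of about 0.11, 0.28 and 0.54.

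**Alternatives.** If a recruiter steers every patient on the best guess, with success rate g and the same 70%/50% groups, the false difference is 20·(2g − 1) points. A big-stick design with limit b forces about 1/(2b) of the slots, and g = (1 + forced share)/2. The figures for varying blocks come from simulating an optimal guesser who does not know the current block size.

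| Scheme | Certain slots | g | False difference | Type I error |
|---|---|---|---|---|
| Fixed 2 | 50% | 75% | 10 points | 28% |
| Varying 4/6/8, undisclosed | about 2% | about 68% | about 7 points | about 16–17% |
| Big-stick, limit 1 | 50% | 75% | 10 points | 28% |
| Big-stick, limit 3 | about 16% | about 58% | about 3 points | about 7% |

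A limit of 1 forces the next allocation after every imbalance, so it is the same procedure as blocks of 2. A limit of 2 still forces about 25% of slots.

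**The case against.** The best defence is that the article already places code release after the eligibility check and uses a randomization system. For the first woman of each pair that works, since her arm cannot be known. A reader might infer from the block size that allocation is not concealed at all. The article does not support that: 91 of the 182 slots are random and released in the right order. The safeguard fails only for the second slot, where the arm can be deduced without opening the system.

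Second, the 28% needs a recognisable 20-point prognostic gap and steering in every known slot. The article gives no such gap, and with a quarter of the slots steered the error is close to nominal. This stands: the figures show what the design permits, not what is expected. The direction is also open. Clinicians might favour the supplement for higher-risk women, which would dilute a true benefit rather than create a false one.

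Third, the plan includes baseline summaries by arm and a multivariable logistic model. These could reveal and partly adjust for steering on recorded factors. They do not reach unrecorded ones, and they do not change the primary test.

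Fourth, no blocked scheme is free of guessing. That is also true, and the remaining risk should be stated with the fix.

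**Conclusion.** The point holds for the second allocation of every pair: 91 of 182 (50%) can be deduced before eligibility is judged, with a 75% best-guess rate. That part is arithmetic. It rests on a recruiter knowing the previous allocation and the position in the list, which is realistic for three unblinded colleagues at one site drawing from one list.

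Selection bias is possible in either direction. Under the assumed 70%/50% split its size runs from 2.5 points (type I error about 6%) to 10 points (about 28%), set against the 20-point effect that the trial is powered to detect. A reader might go further and conclude that the trial will be biased in favour of Moducare, or that larger blocks remove the problem. Neither follows: nothing in the article shows steering or its direction, and every alternative considered leaves some predictability. The change is still needed before enrolment, because it is cheap now and bias in how the arms were formed cannot be undone later.

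**What to change.** Before the first patient (planned for 01/06/2026), regenerate the list and replace the sentence that fixes the block size. Two options:

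- randomly varying permuted blocks, for example 4, 6 and 8, with the sizes withheld from the recruiting clinicians and not published until enrolment ends; or
- a big-stick design with a stated imbalance limit of at least 3. The limit must be written down, because a limit of 1 reproduces the present scheme.

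Under either option, have the system release the arm only after the woman has been irrevocably registered as eligible. Add selection bias to the limitations in the Discussion, with the predictability that remains. Varying blocks remove nearly all certain slots but leave a guess rate of about 68%; a big-stick limit of 3 leaves about 16% forced slots but a guess rate of about 58%.

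The cost is a new list, one changed sentence and one amendment, which the Statement of ethics says needs new Institutional Review Board approval. The final arm sizes may differ by a few patients, with negligible loss of power. The total of 182 stays.

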### Study timeline

Patient enrollment is expected to start in the second quarter (Q_2_) of 2026 (01/06/2026). Before enrollment all patients will sign a written informed consent. Trial duration is estimated at twenty-four months, while participant recruitment is expected to last for twelve months [approximately the second quarter of 2027 (31/05/2027)]. The primary endpoint, regression rate of low-grade cervical intraepithelial neoplasia (CIN1), is expected to be reached after six months from last patient enrollment. Moreover, for the secondary endpoints: regression rate of CIN1 is expected to be reached after twelve months from last patient enrollment, while progression rate of CIN1 will be evaluated at two timepoints, after six and twelve months from last patient enrollment. The safety analysis include the investigation of the six-month intervention (Moducare) related adverse events, which will be assessed at six months from last patient enrollment of arm B. In conclusion, data collection is set to be completed in the second quarter of 2028 (31/05/2028), while the preliminary results are expected at the end of 2027 (01/12/2027) with the final results at the second quarter of 2028 (31/06/2028).

